An innovative proposal to overcome these limitations is the development of meta-instruments, understood as integrated assessment instruments that combine items and constructs from multiple validated tools into a single parsimonious instrument while maintaining clinimetric properties and diagnostic capacity equivalent to those of the original tools [29]. For instance, the VALENF Instrument [30,31] is a predictive algorithm that estimates functional capacity, pressure injury risk, and fall risk by merging the Barthel, Braden, and Downton scales into a seven-item solution. This meta-instrument has shown high predictive accuracy and reliability for the original scales’ total scores, along with adequate clinimetric properties.

Adapting this approach to hospital-at-home care could optimize nurses’ time, enhance the early detection of risks, and promote the standardization of care [16]. Therefore, it seems pertinent to develop and validate a specific meta-instrument for hospital-at-home settings aimed at supporting more parsimonious, standardized, and person-centred nursing practices. This instrument, named VALENF-HAD (from the Spanish VALoración ENFermera–Hospitalización A Domicilio, meaning “Nursing Assessment – Hospital-at-Home”), is designed to integrate multiple dimensions of nursing assessment in hospital-at-home settings, including functional capacity, pressure injury risk, fall risk, frailty, nutritional status, and sleep quality.

The overall objective of this study is to develop and validate a meta-instrument (VALENF-HAD) that integrates the assessment of functional capacity, pressure injury risk, fall risk, frailty, nutritional status, and sleep quality in patients admitted to hospital-at-home units based on the analysis of validated nursing assessment instruments. Specifically, the study aims to identify patient profiles with similar care needs based on nursing assessment, analyse the influence of sociodemographic and care-related variables on assessment outcomes, examine the relationships among the included instruments to identify redundant items, and determine the clinimetric properties of the VALENF-HAD meta-instrument, including content validity, construct validity, and internal consistency.

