### Statistical analysis

The statistical analysis will be conducted in four sequential phases. First, the sample and measurement instruments will be characterized through a descriptive analysis according to the nature of the variables. Significant differences in the assessment results of problems related to hospitalization will be examined, considering sociodemographic and care process variables, taking into account whether the data are patient self-reported or proxy-reported. The normality and homoscedasticity of the sample will be tested using the Kolmogorov–Smirnov and Levene tests, respectively. Depending on the results, Student’s t test or ANOVA will be applied, depending on the number of groups. Categorical variables will be analysed using the chi-square (χ²) test, and correlations will be assessed using Pearson’s or Spearman’s test, as appropriate. When the assumptions for these tests are not met, the corresponding nonparametric tests will be applied.

Following this initial analysis, the development and validation process of the new meta-instrument will be carried out by adapting the methodological proposal of Llagostera-Reverter et al. [29]. First, an analysis will be performed to explore the conceptual and semantic relationships among the dimensions of the instruments. In addition, the items of the instruments will be analysed to identify similarities, duplications, and redundancies, with the goal of establishing direct or indirect conceptual relationships through a nominal group [43] composed of members of the research team and nursing professionals working in home hospitalization units and analysing nursing physical care within the conceptual framework of the Fundamentals of Care [44]. Subsequently, conceptual similarities and redundancies between the dimensions and items of the instruments will be examined, and correlations will be tested using Pearson’s or Spearman’s tests, as appropriate. Multiple correspondence analysis and cluster analysis will be used to explore potential groupings of items and to identify clinical profiles of patients with similar care needs [45–47].

Second, linear model analyses will be performed using each assessment instrument as a dependent variable to determine the influence of sociodemographic and care process variables. Additional linear model analyses will be conducted to predict the scores of the original instruments on the basis of combinations of their own items.

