Third, the initial validation of the new meta-instrument will be conducted. Agreement will be assessed using the intraclass correlation coefficient (ICC > 0.7) [48]. Participants will also be grouped according to the categorical levels of each assessment instrument on the basis of their obtained scores, and overall and category-specific agreement will be examined using Kendall’s tau-b and Cohen’s kappa tests (τ-b and κ > 0.7) [49]. To ensure the robustness and generalizability of these predictive models, cross-validation will be applied [50].

Fourth, the clinimetric properties will be determined following the recommendations of the COSMIN initiative [51]. Content validity will be evaluated through a nominal group of clinical nurses with at least 10 years of experience and university nursing faculty with doctoral degrees. They will assess the relevance of the proposed items and dimensions using the Polit and Beck (2006) methodology to calculate the item-level content validity index (I-CVI ≥ 0.78) and the scale-level content validity index (S-CVI ≥ 0.9) [52]. Construct validity will be assessed according to the methodology proposed by Efron and Tibshirani [53]. The sample will be randomly divided into two subgroups. In the first subgroup, an exploratory factor analysis with oblimin rotation and maximum likelihood estimation will be performed after verifying adequacy through Kaiser–Meyer–Olkin and Bartlett’s sphericity tests. In the second subgroup, confirmatory factor analysis and structural equation modelling will be conducted to validate the theoretical structure of the instrument. Model fit will be evaluated using χ²/df (<5), RMSEA (<0.05), and CFI (≥0.97). Internal consistency will be estimated using McDonald’s Omega (Ω > 0.7) [54] and Cronbach’s alpha (α > 0.7), as appropriate, depending on the characteristics of the data and the underlying assumptions of each method [55]. Finally, interrater reliability will be assessed in a pilot sample using the intraclass correlation coefficient (ICC > 0.61). A p value < 0.05 will be considered to indicate statistical significance, and analyses will be conducted using software, selected according to their specific analytical capabilities for descriptive, multivariate, and advanced modelling procedures.

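### The phase-three acceptance rule (ICC, tau-b and kappa above 0.7) can be met while a sizeable share of a minority high-risk group is missed

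*Protocol article*

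**What the plan says.** The protocol article builds the meta-instrument by regression. Its Statistical analysis section states: "Additional linear model analyses will be conducted to predict the scores of the original instruments on the basis of combinations of their own items".

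Phase three of that section then sets the acceptance rule:

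- For scores: "Agreement will be assessed using the intraclass correlation coefficient (ICC > 0.7".
- For categories: "Participants will also be grouped according to the categorical levels of each assessment instrument on the basis of their obtained scores", after which "overall and category-specific agreement will be examined using Kendall’s tau-b and Cohen’s kappa tests", with the threshold "τ-b and κ > 0.7".
- For stability: "To ensure the robustness and generalizability of these predictive models, cross-validation will be applied".

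The Background sets the standard to be met. It defines a meta-instrument as a reduced tool "maintaining clinimetric properties and diagnostic capacity equivalent to those of the original tools". The Abstract names early detection of risk as an expected benefit.

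The article does not say which cut-off is applied to the predicted scores. It gives numerical thresholds for ICC, tau-b and kappa, and none for sensitivity, specificity or predictive values.

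**The concern.** The stated criteria do not measure the property claimed. Diagnostic capacity is directional: a patient whom the original scale flags and the new tool does not is a different error from a false alarm.

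- **Tau-b** measures ordinal association. It can stay high when patients are systematically placed in too low a level.
- **Kappa** corrects agreement for chance but is unchanged when the missed and falsely flagged cells are exchanged.
- **ICC** on the whole score range is driven by the bulk of patients and says little about one cut-off.

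Where the at-risk level is a minority, the many correctly classified low-risk patients can carry these measures past 0.7 while many at-risk patients are missed. There is also a tendency in one direction: a least-squares prediction has less spread than the score it predicts, so a fixed cut-off in the tail captures fewer patients.

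At stake is what a pass would allow the authors to say. VALENF-HAD could meet every published threshold and be called equivalent, with nothing in the rule showing how many at-risk patients it fails to find.

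**Working it through.** **The plan's own figures.** The article states no expected sensitivity, specificity, R² or kappa, so there is nothing of that kind to reproduce. Its sample size does reproduce: 59 items × 10 = 590, doubled to 1,180.

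**Inputs.** From the article: linear prediction of the original scores, the 0.7 thresholds, n = 1,180. Assumed here: standard normal scores, R², the prevalence p of the high-risk level, two levels, unweighted kappa, and the original cut-off applied unchanged to the prediction.

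**Model.** Let Y be the original score and Ŷ = E[Y | items]. Then Var(Ŷ) = R², Cov(Y, Ŷ) = R², corr = √R².

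- ICC (absolute agreement) = 2R² / (1 + R²)
- Cut-off c = Φ⁻¹(p), with the worst scores below c
- Predicted prevalence q = Φ(c / √R²)
- b = P(Y < c and Ŷ < c), bivariate normal
- Sensitivity = b/p; specificity = (1 − p − q + b)/(1 − p)
- κ = (po − pe)/(1 − pe), with po = 1 − p − q + 2b and pe = pq + (1 − p)(1 − q)
- For two levels, tau-b = (b − pq)/√[p(1 − p)q(1 − q)]

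**Worked case, R² = 0.90, p = 10%.** ICC = 1.80/1.90 = 0.947. q = 0.0884 and b = 0.0723. Sensitivity = 0.0723/0.10 = 72%; specificity = 98%. po = 0.956, pe = 0.829, κ = 0.74; tau-b = 0.75. All thresholds pass. With n = 1,180 there are 118 high-risk patients. About 33 are missed (0.10 − 0.0723 = 0.0277; × 1,180) and about 19 are falsely flagged (0.0884 − 0.0723 = 0.0161; × 1,180).

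**Range.**

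| R² | p | ICC | κ | tau-b | Sensitivity | Predicted prevalence | All > 0.7? |
|---|---|---|---|---|---|---|---|
| 0.90 | 5% | 0.95 | 0.71 | 0.71 | 66% | 4.2% | yes |
| 0.90 | 10% | 0.95 | 0.74 | 0.75 | 72% | 8.8% | yes |
| 0.85 | 20% | 0.92 | 0.72 | 0.72 | 73% | 18.1% | yes |
| 0.90 | 30% | 0.95 | 0.79 | 0.79 | 84% | 29.0% | yes |
| 0.90 | 50% | 0.95 | 0.80 | 0.80 | 90% | 50.0% | yes |
| 0.90 | 70% | 0.95 | 0.79 | 0.79 | 94% | 71.0% | yes |
| 0.85 | 10% | 0.92 | 0.68 | 0.68 | 65% | 8.2% | no |
| 0.80 | 10% | 0.89 | 0.62 | 0.63 | 57% | 7.6% | no |

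**How much is shrinkage?** At R² = 0.90 and p = 10%, moving the cut-off so that q = p removes the shift. Sensitivity rises from 72.3% to 77.6%, specificity falls from 98.2% to 97.5%, and κ moves only from 0.744 to 0.752. So about 5 of the 28 missed points come from shrinkage; the other 22 or so are ordinary prediction error. Kappa hardly registers the change.

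**Does agreement per category catch it?** Not necessarily. With three levels of 60/30/10% and R² = 0.88, simulation gave ICC 0.94, overall κ 0.71, tau-b 0.79 and top-level κ 0.72, with sensitivity 69.5%.

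**Does cross-validation catch it?** In an item-level simulation (10 ordinal items at loading 0.70, n = 1,180, 10-fold cross-validation, high-risk prevalence about 9%), a five-item prediction passed every criterion in 68% of runs, with sensitivity 69% in those runs. A three-item prediction passed in 4%.

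**Tau-b alone.** Take three equal levels, with every middle and high patient placed one level too low. Of the three between-level pairings, two are concordant and one is tied on the prediction, so tau-b = 2/√(3 × 2) = 0.82. Observed and chance agreement are both 1/3, so κ = 0. Tau-b passes with 67% misclassified; κ rejects the case.

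**The case against.** **The cut-off rule is inferred.** The article speaks of grouping on obtained scores and does not say that the original cut-offs are applied unchanged to predictions. That stands. It remains the natural reading, because agreement with the original levels requires a second set of levels from the prediction. The argument about symmetric criteria does not depend on it.

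**A full analysis plan exists and may add accuracy measures.** It may, and their absence from an article is not in itself an error. The point is narrower: the article does publish its validation thresholds, and those do not test the property that its Background requires.

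**A reader might infer that the tool will under-detect and still pass.** The documents do not support that. Under-detection through shrinkage needs an at-risk prevalence below 50%; above it the rule over-detects. The article gives no prevalence, and in a multimorbid population some at-risk levels may be common. Nor is passing assured: at R² 0.80 and 10% prevalence κ is 0.62 and fails, and the tau-b example fails because its κ is 0. The plan requires both measures.

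**A reader might also blame reuse of the original cut-offs for most of the loss.** The working does not support that either: prevalence matching recovers only about 5 of 28 points.

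**Safeguards exist.** "overall and category-specific agreement will be examined" is planned, as is cross-validation. Both help, but the first still rests on the same measures and the second corrects optimism, not the choice of criterion. Item-level data are to be shared, so sensitivity could be computed later, but only after the validation claim had been made.

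**Conclusion.** The point holds in limited form. The published rule can be satisfied while roughly a quarter to a third of a minority high-risk group is missed: 28% at 10% prevalence and 34% at 5%, both at R² 0.90. No stated criterion would show it, so a pass would not establish equivalent diagnostic capacity.

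The size rests on assumed normality, R², prevalence, two levels, unweighted kappa and unchanged cut-offs, none of which the article gives. The structural point needs none of these: the criteria do not distinguish missed from falsely flagged patients.

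This is an inexpensive improvement to the acceptance rule. It does not show that the instrument will fail.

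**What to change.** In phase three of the Statistical analysis section, before analysis begins (planned for 01/09/2026):

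1. Add to the acceptance criteria, for each instrument's at-risk level, sensitivity, specificity and positive and negative predictive values with 95% CI, computed from the cross-validated predictions. State in advance what values count as acceptable.
2. Compare predicted with observed prevalence of each level. Where they differ, set the predicted-score cut-off inside the training folds so that prevalence matches, and state the rule.
3. Keep tau-b as a description of association, not as an agreement criterion.

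A cut-off fixed at some high sensitivity, direct modelling of the categories and weighted kappa are options with their own trade-offs; the point does not require them.

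**Cost.** No new data, slightly more output, and headline performance that may look less favourable. Precision will be moderate for rare levels: with 118 high-risk patients and sensitivity 0.72, the 95% half-width is 1.96 × √(0.72 × 0.28/118) = 0.08.

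### The content-validity step rates only the relevance of the items put forward, so it cannot show whether cutting down 59 pooled items removed essential content

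*Protocol article*

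**What the plan says.** All references are to the protocol article.

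- **Aim of the reduction (Background).** The study will "examine the relationships among the included instruments to identify redundant items". A meta-instrument is described there as combining items from several validated tools while "maintaining clinimetric properties and diagnostic capacity equivalent to those of the original tools". Content validity is listed among the properties to be determined.
- **Item pool (Participants and sample).** The instruments together hold 59 items.
- **First review (Statistical analysis).** A nominal group "composed of members of the research team and nursing professionals working in home hospitalization units" looks for similar, duplicated and redundant items, "analysing nursing physical care within the conceptual framework of the Fundamentals of Care".
- **Third phase.** Agreement with the original instruments is tested by ICC on scores and by tau-b and kappa on categories, each above 0.7, with cross-validation.
- **Fourth phase.** The section says that "the clinimetric properties will be determined following the recommendations of the COSMIN initiative". For content validity the raters are "a nominal group of clinical nurses with at least 10 years of experience and university nursing faculty with doctoral degrees". Their task is stated in one sentence: "They will assess the relevance of the proposed items and dimensions using the Polit and Beck (2006) methodology". The criteria are an I-CVI of at least 0.78 and an S-CVI of at least 0.9.

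**The concern.** An instrument made by deleting items can fail on content in two ways: it may keep something irrelevant, or it may lose something that matters. The rating described addresses the first. For a tool assembled from validated scales, the second is the more specific hazard. An item may be dropped because its parent score can be predicted without it, although a nurse would regard it as essential.

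The Abstract places this rating in phase IV, after design and initial validation, so the natural reading is that the proposed items are those of the reduced instrument. A favourable S-CVI would then probably be read as evidence that the content of the original scales was preserved, which the index does not measure.

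A smaller matter is who rates. The fourth-phase criteria mention length of experience or a doctorate but not the care setting. The first nominal group explicitly includes nurses from these units, and the Background stresses how far home nursing departs from hospital nursing.

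**Working it through.** **The plan's own figure.** 59 items × 10 assessments per item = 590, and the final 1,180 = 59 × 20. Both reproduce and are not in dispute. The content-validity cut-offs are fixed thresholds, not derived figures.

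**Step 1: what the indices depend on.**
- I-CVI for an item = experts rating it relevant ÷ experts rating it.
- S-CVI = either the mean of the I-CVIs or the share of rated items on which all experts agree.

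Neither formula contains a term for an item that was not rated. As an illustration (my assumption), take six domains with three items each, every I-CVI being 0.95:
- all 18 items: (18 × 0.95) ÷ 18 = 0.95;
- one item dropped from each domain: (12 × 0.95) ÷ 12 = 0.95;
- a whole domain dropped: (15 × 0.95) ÷ 15 = 0.95.

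The index does not respond to omission.

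**Step 2: how many items might go unrated.** The article does not fix the final length. With 7 items, the size of the earlier VALENF, (59 − 7) ÷ 59 = 88% would go unrated. With 15 items (an assumption), (59 − 15) ÷ 59 = 75%. The earlier tool merged three scales and this one covers seven, so 7 may be too low. Unrated also does not mean wrongly lost, since removing redundancy is the purpose.

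**Step 3: how much the third phase protects.** For a calibrated linear prediction, the covariance of predicted and observed scores equals R² times the observed variance, and the variance of the predictions is the same quantity. Hence

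ICC = 2R² ÷ (1 + R²), so R² = ICC ÷ (2 − ICC).

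At the threshold, R² = 0.7 ÷ 1.3 = 0.538. A simulation with R² set at 0.54 gave an ICC of 0.698, which agrees. The ICC criterion alone can therefore be met with about 1 − 0.538 = 46% of an original score's variance unexplained. The tau-b and kappa criteria may be harder to meet, but they also compare results rather than content. An item that rarely varies adds little to any of these measures, whatever its clinical importance.

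**Step 4: can the relevance rating itself fail?** With 5, 6, 8 or 10 experts, an I-CVI of at least 0.78 needs 4, 5, 7 or 8 endorsements. The article gives no panel size, so I assumed 5 to 10 experts, 7 to 25 items, independent ratings and the averaging form of S-CVI. The probability that every item passes and the mean reaches 0.9 is then:

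| Chance that an expert endorses an item | Probability of passing |
|---|---|
| 0.80 | about 0–5% |
| 0.90 | 0.5–48% |
| 0.95 | 23–91% |
| 0.98 | 77–99% |

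The criteria are real tests of relevance. They are not tests of coverage.

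**The case against.** The strongest reply is that the plan does not leave loss of content unguarded. The first nominal group, with hospital-at-home nurses in it, works through the items within a care framework. The objective fixes the six domains. The third phase checks agreement instrument by instrument, on scores and categories, so losing an element that drives the nutrition, sleep or fall-risk result should show there. The panel rates dimensions as well as items. COSMIN is named as the guide and may bring wider content work in the full protocol. All of this stands, and it makes the gap partial. What remains is that the first group looks for redundancy before the modelling, so it does not judge the final selection; the third phase compares scores; and the only content judgement described for the finished tool is relevance.

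Three stronger readings are tempting but not supported:

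- **That the index will pass almost automatically.** Items from validated scales may well be rated highly, but the pass probability runs from about 0% to 99% over the endorsement rates tried. Relevance to this setting is not guaranteed by relevance elsewhere.
- **That the panel rates its own selection.** The article neither requires nor excludes overlap between the two groups, and the first group is not said to choose the final items. A condensed article may leave this to the full protocol.
- **That the panel will lack hospital-at-home experience.** The criteria do not demand it, but they do not exclude it either.

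**Conclusion.** The point holds in a limited form. As described, the content-validity step measures the relevance of what is put forward, and its indices cannot register what was removed. This follows from the formulas and does not depend on panel size, final length or the version of S-CVI. It rests on reading the proposed items as those of the reduced instrument, which the order of the phases supports. The safeguards elsewhere are partial: the ICC criterion alone tolerates about 46% unexplained variance under a calibrated linear prediction, and no agreement statistic judges coverage. How much content would actually be lost cannot be estimated from the article; the 75–88% in Step 2 describes unrated items, not harm. This is an inexpensive improvement that changes what the content-validity claim can support. It does not invalidate the design.

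**What to change.** Keep the planned fourth-phase panel and thresholds, and extend the task:

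1. Show the dropped items beside the retained ones, grouped by the six domains.
2. Have raters judge the relevance of the dropped items too, and the coverage (comprehensiveness) of each domain by the retained set.
3. Report as content loss any dropped item with an I-CVI of at least 0.78 that has no retained counterpart in its domain.
4. Preferably include clinical raters with hospital-at-home experience, as the first nominal group does.

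The change touches no patient data, and analysis is scheduled to start on 01/09/2026. The costs are a longer rating form, some narrowing of the pool of clinical raters if the fourth item is adopted, and a content-validity result that may look less favourable.

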### Participants and sample

The study population will consist of nursing assessments performed on adult patients receiving Hospital-at-Home care in four public hospitals in the province of Castellón (Spain), which together provide health care coverage to 615.188 people: Hospital Universitario Comarcal de Vinaròs (HUCV), Hospital Universitario de La Plana (HULP), Consorcio Hospitalario Provincial de Castellón (CHPC), and Hospital General Universitario de Castellón (HGUCS).

The study will include nursing assessments conducted within the first 48 hours after admission for patients aged 18 years or older who agree to participate and provide written informed consent, as the assessment instruments included in the study are primarily validated in adult populations. The first hours were selected because they correspond to the initial nursing assessment period in hospital-at-home units, allowing for a standardized baseline evaluation. Assessments from patients whose expected stay is less than 48 hours, such as those admitted under a day hospital regimen, will be excluded.

Regarding sample size, the literature recommends including between 5 and 10 participants per item in studies aimed at the development and validation of questionnaires [32]. The total number of items across all the instruments considered in this study is 59; therefore, a minimum of 590 assessments was initially estimated. However, due to the lack of specific recommendations for studies involving the integration of multiple assessment instruments and based on previous methodological references [29], the sample size was increased to 1.180 assessments to ensure adequate representativeness and to support more complex analytical strategies.

The sample will be stratified according to the number of admissions in each HaH unit, excluding 20% corresponding to day-hospital admissions. Consecutive sampling will be performed in each until the required sample size is reached, as shown in Table 1.

**Table 1 pone.0351126.t001:** Sample size estimation.

Hospital	Admissions in 2022	Average monthly admissions	Estimated n (12 months)
HUCV	1.136	94	318
HULP	1.105	92	311
CHPC	889	74	251
HGUCS	1.066	88	300
**TOTAL**	4.196	348	**1.180**

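### Maximum likelihood is fixed for the exploratory factor analysis whatever the item type; with unevenly distributed categorical items this can distort the factor structure

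*Protocol article*

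**What the plan says.** The fourth phase in the Statistical analysis section of the protocol article covers construct validity. The plan there is: "The sample will be randomly divided into two subgroups". In the first subgroup, after the Kaiser–Meyer–Olkin and Bartlett checks, "an exploratory factor analysis with oblimin rotation and maximum likelihood estimation will be performed". For the other half, "In the second subgroup, confirmatory factor analysis and structural equation modelling will be conducted to validate the theoretical structure of the instrument". The criteria follow: "Model fit will be evaluated using χ²/df (<5), RMSEA (<0.05), and CFI (≥0.97".

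Maximum likelihood is therefore stated for the exploratory half. The confirmatory half has cut-offs but no named estimator. The section names no correlation matrix for the factor analysis and no rule for the number of factors.

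Earlier in the same section, "Multiple correspondence analysis and cluster analysis will be used to explore potential groupings of items". That method is meant for categorical variables. The section makes the choice of method depend on the data for group comparisons, for correlations and for omega or alpha, but not for the factor analysis.

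**The concern.** Normal-theory maximum likelihood assumes continuous, multivariate normal variables. When binary or few-category items enter it through product-moment correlations, each correlation is limited by how similarly the two items are distributed. Items that are common and items that are rare then correlate less with each other than within their own group. The analysis can read that pattern as an additional dimension, and the loadings shrink. The misfit also feeds into χ² and the indices built on it.

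Construct validity is one of the clinimetric properties named in the study objective. A sound instrument could be given a dimension it does not have. If the same estimator is used in the confirmatory half, the instrument could be judged structurally inadequate for reasons that have nothing to do with its structure.

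**Working it through.** **Sample size per half.** The article counts items ("The total number of items across all the instruments considered in this study is 59"), takes "between 5 and 10 participants per item in studies aimed at the development and validation of questionnaires", and then says "the sample size was increased to 1.180 assessments". 59 × 10 = 590 and 2 × 590 = 1,180, so its figures reproduce. Equal halves (an assumption) give n = 590 for each factor analysis.

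**Mechanism.** Take two binary items with prevalences of 15% and 85%. The joint proportion cannot exceed 0.15. The largest possible product-moment correlation is (0.15 − 0.15 × 0.85) / (0.15 × 0.85) = 0.15/0.85 = 0.18, however closely the underlying traits agree. Two items with equal prevalence have no such ceiling.

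**How the cut-offs relate.** RMSEA = √[max(χ² − df, 0) / (df(N − 1))]. At N = 590:
- RMSEA < 0.05 requires χ²/df < 1 + 589 × 0.0025 = 2.47.
- χ²/df < 5 corresponds only to RMSEA < √(4/589) = 0.082.

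The χ²/df limit is therefore redundant once RMSEA is applied. RMSEA and CFI decide, where CFI = 1 − max(χ² − df, 0) / max(χ²₀ − df₀, χ² − df, 0) and the subscript 0 marks the independence model.

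**Simulation.** In every case the fitted structure is the true one, n = 590, and normal-theory maximum likelihood is applied to Pearson correlations of categorised normal variables. There were 300 data sets per setting (80 for 24 items). Item formats, item numbers, loadings and a factor correlation of 0.4 are assumptions. The seven-item case uses the length of the earlier VALENF Instrument given in the Background.

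| Items | Factors | Loading | Mean RMSEA | Mean CFI | All three met |
|---|---|---|---|---|---|
| 12 binary, 10–20% and 80–90% | 1 | 0.80 | 0.116 | 0.73 | 0% |
| 12 binary, within 20–80% | 1 | 0.80 | 0.065 | 0.94 | 0.3% |
| 7 mixed 2/3/4-category, varied skew | 1 | 0.70 | 0.070 | 0.931 | 5% |
| 12 mixed, varied skew | 2 | 0.70 | 0.045 | 0.939 | 3% |
| 12 mixed, varied skew | 1 | 0.85 | 0.155 | 0.772 | 0% |
| 24 mixed, varied skew | 3 | 0.70 | 0.035 | 0.930 | 0% |
| 12 three-category, same skew | 1 | 0.85 | 0.024 | 0.995 | 100% |
| 12 binary, all 50% | 1 | 0.85 | 0.030 | 0.991 | 100% |
| 12 continuous | 1 | 0.85 | 0.008 | 0.999 | 100% |

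In the first row the true loading of 0.8 was estimated at 0.46 to 0.55 on average. For prevalences within 20–80% the result depends on their arrangement and on the loading. At loading 0.8 the pass rate was 0.3% in one arrangement and 15% with an even spread. At loading 0.7 it was 66% and 88%.

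Across all settings with uneven or opposing skew in the wider grid (7, 12 or 24 items, 1 to 3 factors, loading 0.70 or 0.85), 0% to 19% of samples met all three cut-offs. For symmetric or similarly skewed items the figure was 97% to 100%. CFI is the cut-off missed most often.

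**Spurious factor, same uneven items.** An eigenvalue-above-1 rule added a factor in 72% to 100% of samples. The maximum likelihood χ² test rejected the true number of factors in 87% to 100%. Parallel analysis ranged from 0% to 100%: 0% to 4% with seven items at loading 0.70, and 61% to 100% with 12 items and one factor.

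**Does the alternative work?** Polychoric correlations with diagonally weighted least squares and an adjusted χ² (7 items, 1 factor, 150 data sets) met all three cut-offs in 92% to 99% of samples for the uneven item types. At loading 0.70, maximum likelihood gave 0% to 11% for the same types. The asymptotic covariance in this comparison was taken from the simulation itself, so it shows the principle and not the exact performance of any one package.

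**The case against.** The strongest reply is that much of the harm rests on things the article does not say. It ties maximum likelihood to the exploratory half only, and the fit cut-offs belong to the confirmatory half. A reader might infer that the plan as written will reject a true structure, but that holds only if the estimator is carried over. An estimator left to a fuller analysis plan is not in itself a fault of an article. This stands, and it makes the part about the cut-offs conditional.

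The correlation matrix is not named either. Maximum likelihood on a polychoric matrix is not excluded, although its ordinary χ² would still not be valid. The response formats are not printed, and the items of the meta-instrument are not yet chosen. The simulated prevalences are constructed; with benign distributions the problem nearly vanishes. How often a false factor appears depends on a retention rule that the article does not give. All of this stands as a limit on size.

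A reader might also infer that items would be discarded for being rare or common. The text does not support this. Redundancy is examined by nominal group, correlations, correspondence and cluster analysis and linear models, and no rule removes items on their loadings. Agreement with the original scales (ICC, tau-b, kappa) does not rest on the factor model.

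One thing is left after these concessions. The exploratory estimator is a stated choice, not an omitted detail. It carries no condition on item type, and the plan's own use of correspondence analysis points to categorical items. The Kaiser–Meyer–Olkin and Bartlett checks do not detect the problem.

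**Conclusion.** The point holds in a conditional form, at moderate severity. The article fixes maximum likelihood for the exploratory factor analysis regardless of item type. Attenuated loadings and a spurious factor can follow if three assumptions are met: the items are binary or short ordinal, product-moment correlations are used, and item frequencies are very unequal. Failure of RMSEA < 0.05 and CFI ≥ 0.97 by a true structure needs a fourth: that maximum likelihood is also used in the confirmatory half.

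At n = 590 the pass rate runs from 0% with strongly opposing prevalences to about 100% with symmetric or similarly skewed items. Where the real items will fall cannot be read from the document. Pooling six constructs in patients with widely differing care needs makes uneven frequencies plausible but does not establish them. The sample-size figures are unaffected.

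**What to change.** In the construct-validity paragraph of the Statistical analysis section:

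- Whenever the retained items are binary or short ordinal, replace maximum likelihood in the exploratory analysis with extraction from the polychoric or tetrachoric correlation matrix by weighted or unweighted least squares. Keep the oblimin rotation.
- Fit the confirmatory and structural models with a categorical estimator (WLSMV/DWLS), and apply the cut-offs to its adjusted fit indices.
- Keep maximum likelihood as a sensitivity analysis.

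This costs one or two sentences and needs no new data; the software is standard. Sparse response categories may need collapsing, which is a small downside. The article schedules data analysis from 01/09/2026, so the change can be recorded before then.
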